**Other measures**

***Demographic characteristics***

The participants will be asked about their age (in years), sex (male, female), ethnicity (Han, others), employment status (students, unemployed, employed), education level (Junior high school or below, senior high school or equivalent, bachelor degree or equivalent, master degree or above), marital status (married/living with a partner, unmarried/divorced/separated/widowed), and monthly income (≤3000, 3001-5000, 5001-7000, 7001-10000, 10001-15000, 15001-20000, >20000 CNY). Income is further recoded into a binary variable using 3000 CNY (approximately 700 USD) as a threshold as it is the national average monthly income in China.

***Sexual behaviors***

The participants’ sexual behaviors are measured, including whether having had chemsex (Yes/ No), number of sexual partners, commercial sexual behavior (Yes/ No), roles in sexual intercourse (Insertive/ Receptive/ Versatile), and frequency of condoms use for each intercourse (Never/ Occasionally/ Sometimes/ Often/ Always) in the past follow-up months. For this study, frequency of condom use is re-categorized as inconsistent condom use (Never/ Occasionally/ Sometimes) and consistent condom use (Often/ Always).

***PrEP-related variables***

Regarding the participants’ understanding of PrEP dosing instructions, the ED PrEP users are asked “Which of the following are correct ways to take PrEP on demand?” They could choose responses from: Take 2 pills orally 2 to 24 hours before anticipated sexual activity; Take 1 pill orally 2 to 24 hours before anticipated sexual activity; Take 1 additional pill 24 hours after the initial dose following sexual activity; Take 1 additional pill 48 hours after the initial dose following sexual activity. The daily PrEP users are asked, “Which of the following are correct ways to take PrEP daily. They could choose responses from: Take 1 pill every 24 hours; Take 2 pills every 24 hours; High-risk behavior for HIV should only be undertaken after taking the medication daily for 7 consecutive days. The responses include Yes, No, and Uncertain. Only the participants who selected all the correct options are coded as “having correct PrEP adherence knowledge”.

PrEP-related stigma is measured by the Chinese version of HIV PrEP Stigma Scale (HPSS)[9]. The scale consisted of 11 items (e.g., “Someone taking PrEP would be seen by others slutty). Each item is rated on a 5-point Likert scale ranging from 1 (strongly disagree) to 5 (strongly agree). A summative score ranging from 11 to 55 is calculated by summing the scores of all items. After reverse scoring, a summative score is calculated, with higher total scores indicating greater stigma associated with taking PrEP.

***Social-psychological variables***

Self-efficacy of keeping optimal PrEP adherence is evaluated by an adapted version of the Condom Use Self-Efficacy Scale [10], which has been validated among Chinese MSM populations [11]. The adapted scale included six items related to consistent PrEP use (e.g., “Even if my sexual partner is unwilling, I am confident in continuing PrEP use”). Each item is rated on a 5-point Likert scale, ranging from 1 (strongly disagree) to 5 (strongly agree). A summative score ranging from 6 to 30 is created by adding up the score of each item, with a higher total score indicating greater self-efficacy in adhering to PrEP.

Depressive symptoms are assessed by the Patient Health Questionnaire-9 (PHQ-9) [12], which has been validated in Chinese MSM populations and demonstrated strong psychometric properties [13]. The questionnaire asked participants about the frequency of specific symptoms experienced over the past two weeks, with each item rated on a 4-point Likert scale ranging from 0 (not at all) to 3 (nearly every day). A summative score ranging from 0 to 27 is created by adding up the score of each item.

Psychological resilience is measured by the 2-item Connor-Davidson Resilience Scale (CD-RISC-2) [14], which has been validated among MSM populations [15]. The items included “Able to adapt to change” and “Tend to bounce back after illness or hardship”. Responses are rated on a 5-point Likert scale ranging from 0 (never) to 4 (always). A summative score ranging from 0 to 8 is created by adding up the scores of 2 items.

**3.7 Data Management and Quality Control**

Survey responses are automatically recorded on the Wenjuanxing platform and exported as encrypted files. All datasets are stored on password-protected institutional servers, accessible only to authorized study staff. Each participant is assigned a unique identifier at recruitment, which is used throughout all surveys to ensure anonymity. No personal identifiers are collected or stored.

To ensure data quality, each submission is reviewed for completeness, internal logic consistency, and reasonable completion time. Submissions failing these checks are excluded from analysis and do not qualify for incentives. Logic constraints are built into the questionnaire to minimize careless or contradictory responses.

During data management, double validation procedures are applied at the time of dataset export and cleaning. Backup copies are securely maintained, and audit trails are preserved to document data handling. All analytic datasets used for statistical analyses will be fully anonymized.

**3.8 Statistical Analysis Plan**

All statistical analyses will be pre-specified and conducted according to this plan. Analyses will distinguish between event-driven (ED) and daily PrEP regimen users. Both descriptive and inferential statistics will be used to evaluate adherence and associated factors across baseline, 1-, 3-, and 6-month follow-ups.

**Descriptive Analyses**

- **Baseline characteristics:** Continuous variables (e.g., age, psychosocial scores) will be summarized as means (standard deviations) or medians (interquartile ranges), depending on distribution. Categorical variables (e.g., education, income category, sexual role) will be summarized as frequencies and percentages.
- **Adherence prevalence:** The prevalence of optimal PrEP adherence at each wave will be calculated separately for ED and daily users.
- **Scale Reliability:** Internal consistency of psychosocial measures (e.g., PHQ-9, self-efficacy scale, stigma scale) will be evaluated at baseline using Cronbach’s alpha. Alpha values ≥0.80 will be considered acceptable.

**Regression Analyses**

**Event-driven (ED) users:** Three regression models will be fitted:

- Model 1: A univariable and multivariable generalized linear mixed model (GLMM) with a logit link and random intercept to evaluate factors associated with past three-month adherence using data from baseline, 3-month, and 6-month visits. In the multivariable GLMM, all the exposure variables of interest will be involved.
- Model 2: A univariable and multivariable GLMM with the same structure to evaluate factors associated with past one-month adherence using data from baseline and all follow-up visits.
- Model 3: A logistic regression model for consistent adherence, defined using data from the 3- and 6-month follow-ups, with baseline socio-demographics and averaged time-varying covariates included as independent variables.

**Daily users:** Regression analysis is planned only for past one-month adherence (Model 2), using a GLMM with the same structure as for ED users.

All models will include fixed effects for exposure variables of interest. Univariable GLMMs will be fitted first to estimate crude odds ratios (ORs) and 95% confidence intervals (CIs) for each covariate. Multivariable GLMMs will then be fitted including all pre-specified, theory-driven covariates—regardless of their univariable associations—to estimate independent effects while adjusting for potential confounding.

Missing data will be handled under a complete case framework. Specifically, missing data are expected to arise primarily from loss to follow-up. No imputation will be performed. GLMM models inherently allow for unbalanced data across repeated measures, and participants with incomplete follow-up will contribute all available observations. Attrition patterns will be described in supplementary analyses.

All analyses will be performed using R (version 4.4.2). Statistical significance will be defined as a two-sided p-value < 0.05.

1. **Ethics and Confidentiality**

The study protocol will be reviewed and approved by the Institutional Review Board of Tsinghua University. All procedures will be conducted in accordance with the ethical standards of the Declaration of Helsinki and relevant national guidelines.

Informed consent will be obtained electronically from all participants prior to enrollment. Consent is obtained through a two-step electronic informed consent process conducted anonymously: first, candidates received the e-consent form via WeChat and are enrolled only after replying “agree to participate”; second, the baseline e-questionnaire began with the same consent text and required click-to-consent (“I agree”) before any survey items are displayed. No names or direct identifiers are collected.

Confidentiality of participant data is strictly protected. Each participant is assigned a unique identification key at recruitment, which is used for all subsequent data collection and analysis. No personal identifiers (e.g., name, phone number, address) are collected. Survey data are stored in encrypted files on secure institutional servers with password protection and restricted access. Only authorized research staff have access to the datasets.

Data sharing will follow institutional and journal requirements. De-identified datasets may be made available to qualified researchers upon reasonable request and approval by the corresponding institutional review board.

1. **Anticipated Challenges/Limitations**

- First, the convenience sampling method used in the study (conveniently choosing Bluedhealth as the recruitment channel and conveniently recruited the participants from Bluedhealth PrEP clients) may cause limited generalization ability and selection bias in the study.
- Second, the reliance on self-reported measures to assess PrEP adherence and other factors may introduce recall and social desirability biases. Besides, because participants are repeatedly surveyed at 1, 3, and 6 months, the follow-up process itself may have heightened their awareness of PrEP adherence and modestly influenced self-reported adherence. This monitoring effect could contribute to overestimation of adherence and should be considered when interpreting our results.
- Third, some other factors potentially associated with PrEP adherence (e.g., risk perception, peer support, prior health service use) are not included in the study and need further investigation.

1. **Dissemination Plan**

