To address this gap, the Real-world E-Consumer Cohort of pre-exposure prophylaxis (RECOPE) is established as the first prospective cohort study targeting individuals purchasing PrEP online in China.

1. **Study Objective:**
2. **Primary Objective**

To evaluate medication adherence among real-world e-consumers of PrEP in China, with a focus on both event-driven (ED) and daily regimens, over baseline and three follow-up visits (1, 3, and 6 months), to identify socio-demogrphic and psycho-behavioral factors associated with PrEP adherence, including self-efficacy, PrEP-related stigma, depressive symptoms, and sexual behaviors (e.g., number of partners, chemsex, condom use, sexual role), and to provide evidence to inform interventions that optimize real-world PrEP effectiveness.

1. **Secondary Objectives**

- To assess the utilization of other HIV-related services (e.g., willingness to use long-acting injectable PrEP, HIV testing behavior)
- To evaluated the factors associated with the utilization of other HIV-related services.

1. **Study Design and Methodology**

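### If time-varying factors enter Models 1 and 2 as single visit-level terms, their odds ratios mix between-person and within-person association and should not be read as independent effects

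*Protocol*

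**What the plan says.** Protocol section 3.8 (Regression Analyses) plans three models for event-driven users.

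- Model 1 is a generalised linear mixed model "with a logit link and random intercept to evaluate factors associated with past three-month adherence", "using data from baseline, 3-month, and 6-month visits".
- Model 2 has the same structure for past one-month adherence, "using data from baseline and all follow-up visits". It is also the only regression for daily users.
- Model 3 is an ordinary logistic regression for consistent adherence, with "baseline socio-demographics and averaged time-varying covariates included as independent variables".

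On how factors enter, the section says only: "All models will include fixed effects for exposure variables of interest". The multivariable mixed models are meant "to estimate independent effects while adjusting for potential confounding". The primary objective lists self-efficacy, stigma, depressive symptoms and sexual behaviours among the factors to study, and is intended "to provide evidence to inform interventions that optimize real-world PrEP effectiveness".

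No person-mean or deviation term is specified for Models 1 and 2. Section 3.8 presents itself as the pre-specified plan.

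**The concern.** A random-intercept logistic model treats each covariate as unrelated to the person's own intercept, that is, to a stable tendency to adhere. For self-efficacy about PrEP use or for depressive symptoms this is doubtful: people who are generally more confident may also be people who generally adhere. When it fails, a single coefficient for a visit-level covariate averages two different quantities: how adherence differs between people with different usual levels, and how it differs within a person between visits when the level is higher or lower than usual.

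Stable traits that were not measured affect the first quantity but not the second. The protocol's limitations section names possible correlates that are not collected (risk perception, peer support, prior service use), and some of these may be stable. A factor that merely marks who adheres could then appear with a clearly raised odds ratio, be labelled an independent effect, and be taken up as something to intervene on. Model 3 does not settle the matter. Its averaged covariates give a between-person contrast, but for a different outcome.

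**Working it through.** **Scale of the study.** The protocol's only design figure is the minimum sample of 424 (section 3.2), and the point does not depend on it. It serves to choose a realistic number of people. Equation (1) with p = 0.60, d = 0.05 and deff = 1 + (11 − 1) × 0.01 = 1.1 needs a population size N, which section 3.2 does not state. Taking N = 2,900, near the 3,000 monthly sales in the rationale:

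n = 1.1 × 2,900 × 0.24 / [(0.0025/3.8416) × 2,899 + 0.24] = 765.6 / 2.1266 = 360.0, and 360.0/0.85 = 423.5, rounded up to 424.

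The figure is reproduced, with about 360 people after loss to follow-up. The split between event-driven and daily users is not given, so 200 and 360 people were both tried.

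**Simulation.**
- From the protocol: 3 visits (Model 1) or 4 visits (Model 2), logit link, random intercept.
- Assumed: the intercept is per participant; intercept 0.5; random-intercept SD 1.5; between-person share of covariate variance (ICC) 0.3, 0.5 or 0.7; between-person OR 1.0, 1.5 or 2.0 per total SD of the covariate (1.0 only at ICC 0.5); within-person OR exactly 1; all visits observed.
- Covariate: x = z + w, with z the person's stable level (variance ICC) and w the visit's departure from it (variance 1 − ICC).
- Outcome: logit P(adherent) = 0.5 + β_B z + β_W w + u, with β_W = 0.
- Each of 150 data sets per setting was fitted by maximum likelihood (15-point quadrature) twice: once with x as a single term, once with the person's mean of x and the deviation from it.

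Results for 360 people and 3 visits (percentage of data sets significant at 5% in brackets):

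| ICC | True between OR | Single-term OR | Split: within OR | Split: person-mean OR |
|---|---|---|---|---|
| 0.3 | 1.5 | 1.08 (18%) | 1.01 (4%) | 1.23 |
| 0.3 | 2.0 | 1.14 (28%) | 1.00 (5%) | 1.49 |
| 0.5 | 1.0 | 1.01 (4%) | 1.01 (4%) | 1.01 |
| 0.5 | 1.5 | 1.17 (39%) | 0.99 (6%) | 1.40 |
| 0.5 | 2.0 | 1.27 (74%) | 0.99 (6%) | 1.68 |
| 0.7 | 1.5 | 1.24 (57%) | 0.99 (7%) | 1.41 |
| 0.7 | 2.0 | 1.47 (95%) | 0.96 (6%) | 1.88 |

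With 4 visits, ICC 0.5 and between OR 2.0, the single-term OR is 1.24 (75%), the within OR 1.00 (5%) and the person-mean OR 1.74.

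Over all settings with a between-person association (200 or 360 people, 3 or 4 visits), the single-term OR averages 1.07 to 1.47 and is significant in 7% to 97% of data sets. The separated within-person OR stays at 0.96 to 1.02, significant in 3% to 7%. With no between-person association, the single-term OR is 0.99 to 1.01, significant in 2% to 5%. The signal therefore comes from the mixing.

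**The weighting.** On the log scale, single = λ × between + (1 − λ) × within. For ICC 0.5 and OR 2.0 in the table, λ = (ln 1.27 − ln 0.99)/(ln 1.68 − ln 0.99) = 0.249/0.529 = 0.47. About half of the between-person log odds ratio passes into the single term.

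**Why the person-mean OR falls short of 2.0.** A mean over T visits has reliability ICC/[ICC + (1 − ICC)/T]. At ICC 0.5 this is 0.75 for T = 3 and 0.80 for T = 4, giving 2^0.75 = 1.68 and 2^0.80 = 1.74, as simulated.

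**The case against.** The main stated aim is to find factors associated with adherence, and one pooled odds ratio per factor is a conventional answer to that. No objective asks whether adherence moves when a factor moves within a person. Knowing which users adhere poorly, a between-person question, can also inform interventions. This stands, and it is why the planned models should be kept. What remains is the wording about independent effects, which goes further than association.

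Visit-level entry is inferred, not stated. Section 3.5 lists psychosocial measures only when describing the baseline questionnaire, and section 3.8 mentions time-varying covariates only in Model 3. Fixed effects for exposures do not rule out person-mean terms. If only baseline values enter Models 1 and 2, nothing is mixed. This also stands, so the point is conditional.

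Every input to the size is assumed, and a within-person OR of exactly 1 is the unfavourable case.

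A reader might infer three stronger things that the document does not support:
- That the repeated visits are wasted without the split. They also serve adherence prevalence at each wave and the definition of consistent adherence.
- That Model 3 conflicts with Models 1 and 2. The protocol never presents them as comparable, and Model 3 has its own outcome.
- That a within-person odds ratio would show what an intervention achieves. Adherence is recalled over the past one or three months while the depression score covers the past two weeks, so adherence may come before the covariate.

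**Conclusion.** The point holds as a conditional one and as a cheap improvement. If time-varying factors enter Models 1 and 2 at each visit as single terms, the odds ratios mix two associations whenever these differ, and nothing else in the protocol separates them. Under the stated assumptions, a factor with no within-person association shows an average OR between about 1.07 (slight, seldom significant) and 1.47 (usually significant). If the within-person and between-person associations are equal, the single term is sound.

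It would be tempting to conclude that the planned models are wrong. They are not: no statement is contradicted, no figure is in error, and a single-term odds ratio is a legitimate association. What it does not support is being read as an independent effect that points to an intervention target.

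**What to change.** 1. State how each time-varying factor enters Models 1 and 2. If baseline values only are meant, say so, and the rest falls away.
2. Keep the planned single-term models as the association analysis, and describe their results as associations rather than independent effects.
3. Pre-specify a supplementary version of Models 1 and 2 that enters each time-varying score or behaviour as the person's mean over the visits used in that model plus the visit's deviation from that mean. Report both odds ratios beside the single-term one.
4. In the daily-user model, limit the split to the key psychosocial scores if the sample is small.

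No new data are needed: a few lines of R and extra table columns. The price is about one more parameter per factor (two for sexual role, which has three categories) and wider within-person confidence intervals. The between-person odds ratio is pulled somewhat toward 1, because means over 3 or 4 visits are noisy. This will be more marked where loss to follow-up, or event-driven users without sex in the period, leave fewer usable visits. The split gives no evidence on direction, and the report should say so.

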**3.4 Recruitment Procedure**

Recruitment will be conducted in collaboration with BluedHealth. Staff from BluedHealth will distribute recruitment materials (texts and posters) containing a unique identification key and contact details. The unique keys will be generated using a four-digit code plus a letter (e.g., 1001c, 1002d), ensuring each participant can be individually tracked.

The first round of recruitment will target individuals who purchased PrEP within one month prior to study initiation. If fewer than 650 participants are enrolled within two weeks, subsequent rounds will expand eligibility to those who purchased PrEP within the past two or three months, until the target sample size is reached (ideally within 30 days).

Recruiters will contact eligible clients through BluedHealth customer service channels or directly at the time of PrEP purchase, inviting them to join the study. Interested individuals will scan a WeChat QR code to connect with study investigators. Prospective participants must include their unique key when adding the investigator to confirm identity. Investigators will verify inclusion/exclusion criteria, obtain informed consent, and finalize enrollment.

A reminder mechanism will be implemented: after receiving the QR code, potential participants will receive up to two reminders within 48 hours. If they do not respond, the key will be invalidated. Each participant’s unique key will serve as their identifier throughout the study(figure 1).

[figure not shown]

Figure 1 Flowchart of the study procedure

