**Primary Outcome**

The primary outcome of this study is PrEP adherence, assessed separately for daily and event-driven (ED) regimen users at each follow-up visit (1, 3, and 6 months after baseline).

- **ED users:** Adherence to ED regimen is assessed by four items. First, the participants are asked whether they had engaged in sexual activity in the past one and three months, respectively (the 1-month follow-up survey only asked this question for the past one month). Those who answer “no” or reported to have never initiated PrEP in a previous question were treated as missing data for PrEP adherence. Those who answer “yes” are then asked if they had taken PrEP for each sexual encounter in the corresponding time period, including those with both primary (e.g., main or long-term partners) and non-primary (e.g., casual or commercial partners) sexual partners (1 = every time, 2 = sometimes, and 3 = never). The participants who choose “every time” or “sometimes” are subsequently asked three adherence questions based on the ‘2-1-1’ dosing guideline: (i) whether (yes or no) they took two pills of PrEP 2 to 24 hours before the sexual activity for each medication (timepoint A); (ii) whether they took one pill 24 hours after the first dose for each medication (timepoint B); and (iii) whether they took another pill 48 hours after the first dose for each medication (timepoint C). The participants who reported to take PrEP for each sexual encounter and chose “yes” to all three adherence questions are classified as “being adherent,” otherwise, they would be classified as “non-adherent.” Lastly, three binary outcome variables are constructed: past 1-month adherence based on baseline and all follow-up data, past 3-month adherence based on baseline and 3- and 6-months follow-up data, and consistent adherence based on 3- and 6-months follow-up data (defined as having optimal past 3-month adherence at both 3- and 6-month follow-up surveys).
- **Daily users:** Adherence to daily PrEP regimen is assessed with a single item: “In the past month, have you ever failed to take PrEP on time and in a correct dosage? (yes/no).” Participants who answer “no” are classified as “adherent,” and those who chose “yes” are categorized as “non-adherent”

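### The event-driven adherence rule is not anchored to first PrEP use, so recent starters can be scored non-adherent at baseline for encounters before they began, and Models 1 and 2 use these scores as outcomes

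*Protocol*

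**What the plan says.** **Who enters.** The inclusion criteria (section 3.3) ask for a BluedHealth purchase and planned use over six months. They neither require nor exclude earlier PrEP use. Under section 3.4, "The first round of recruitment will target individuals who purchased PrEP within one month prior to study initiation"; later rounds may reach back two or three months, and clients may also be approached "directly at the time of PrEP purchase, inviting them to join the study".

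**How ED adherence is scored.** In section 3.6 (Primary Outcome), an ED user with sex in the window is adherent only if PrEP was taken for each encounter in it and all three dosing questions are answered yes. Anything else is non-adherent. The exceptions are people without sex in the window and those who "reported to have never initiated PrEP in a previous question were treated as missing data for PrEP adherence".

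**Which visits count.** The same section opens by saying the outcome is "assessed separately for daily and event-driven (ED) regimen users at each follow-up visit (1, 3, and 6 months after baseline", but then constructs "past 1-month adherence based on baseline and all follow-up data, past 3-month adherence based on baseline and 3- and 6-months follow-up data".

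**How it is modelled.** In section 3.8 (Regression Analyses), Model 1 addresses "factors associated with past three-month adherence using data from baseline, 3-month, and 6-month visits". Model 2 addresses "factors associated with past one-month adherence using data from baseline and all follow-up visits". For daily users, "Regression analysis is planned only for past one-month adherence (Model 2), using a GLMM with the same structure as for ED users".

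**The concern.** A recall window that starts before a person had the drug does not measure adherence in its early part. For an ED user who has just begun, one encounter before the first dose makes it impossible to report PrEP at every encounter, and the rule then returns non-adherent however well the drug was taken afterwards. The missing-data rule removes people who have not started and keeps this group.

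Identifying factors associated with adherence is part of the primary objective. If the baseline score partly records how recently someone began, any factor that differs between new and experienced users can appear related to adherence when it is not. Nothing planned would correct this. The PrEP-related variables in section 3.6 are dosing knowledge and stigma; time since first use is not listed, and the limitations section does not raise the matter. That section does warn that repeated surveys may raise reported adherence, so an artefactual rise from baseline to follow-up could be misread as that monitoring effect.

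**Working it through.** The plan gives no figure on this point. Its assumed adherence of 60% (section 3.2) is used below; every other input not in the protocol is marked as an assumption.

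**1. Share of the baseline window before the purchase.** Let u be the lag in days from purchase to baseline survey and w the window. The share is the mean of max(w − u, 0)/w. Assumption: u is uniform over the range shown.

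| Lag u (days) | 3-month window (w = 90) | 1-month window (w = 30) |
|---|---|---|
| 0 (at purchase) | 100% | 100% |
| 0–30 | 1 − 15/90 = 83% | 1 − 15/30 = 50% |
| 14–44 | 68% | 14% |
| 0–60 | 67% | 25% |
| 0–90 | 50% | 17% |
| 14–104 | 36% | 5% |

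The three-month window lies half or more before the purchase unless lags are long. The one-month window generally does not.

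**2. Chance of a forced non-adherent score.** Take an ED user whose first start is at that purchase, with encounters following a Poisson process at r = 1 to 4 per month (assumption). Given at least one encounter in the window, the chance that one precedes the purchase is mean[1 − exp(−r·max(w − u, 0)/30)] / [1 − exp(−r·w/30)]. For r = 1, u from 0 to 30 and w = 90 this is [1 − (e⁻² − e⁻³)]/(1 − e⁻³) = 0.9145/0.9502 = 96%.

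Someone counted as having initiated will usually also have had an encounter after the purchase, which favours longer lags. Let A = 1 − exp(−r·max(w − u, 0)/30) and B = 1 − exp(−r·min(u, w)/30). The conditioned chance is mean[A·B]/mean[B]; for the same example, 0.3321/0.3679 = 90%.

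| Lag, window | Any encounter in window | Also an encounter in the window since purchase |
|---|---|---|
| 0–30, 3 months | 96–100% | 90–100% |
| 0–90, 3 months | 72–92% | 61–91% |
| 0–30, 1 month | 58–77% | 28–70% |
| 0–90, 1 month | 19–26% | 6–19% |

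The three-month score is forced for most such starters. The one-month score is forced much less often.

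**3. Baseline prevalence.** If a share s of scored ED users are such starters, and a fraction q of them are forced to non-adherent, observed prevalence is 0.6 × (1 − s·q). With s = 10%, 30%, 50% this gives 57%, 51%, 45% for q = 0.5, and 54%, 43%, 32% for q = 0.95.

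**4. Effect on a factor with no true association.** Baseline is one of three planned records per person in Model 1 (one of four in Model 2). Pooling three waves, prevalence at a factor level with new-starter share s is 0.6 × (1 − s·q/3). Take q = 0.8:

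- Share 30% at both levels: 0.552 and 0.552, odds ratio 1.00.
- 20% against 40%: 0.568 and 0.536; odds 1.315 and 1.155; odds ratio 0.88.
- 10% against 50%: 0.584 and 0.520; odds 1.404 and 1.083; odds ratio 0.77.

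A simulation with a person-level random intercept (SD 1.5) gave 1.00, 0.89 and 0.78. With a true effect, a marginal odds ratio of about 1.64 became 1.54 when the factor was unrelated to being new, and 1.35 and 1.15 under the two unequal splits. These are marginal odds ratios, not the planned mixed-model estimates.

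**The case against.** The strongest reply is that the affected group is narrow. A person must be an ED user, have begun before the survey, and have had sex inside the window but before beginning. First-time buyers surveyed on the day of purchase will mostly not have started and are set to missing. Repeat buyers are unaffected when their earlier use reaches back beyond the window, because their time before the purchase is genuine PrEP time. All of this stands. It limits the number affected, which the protocol does not let anyone estimate, but it does not make the score right for those who remain.

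Two stronger readings are tempting and are not supported:

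- *All new starters are scored non-adherent, in both windows and both regimens.* The daily item asks only whether a dose was missed or wrong in the past month, so a recent daily starter with no lapse can answer no and count as adherent. Most of the one-month window generally does not precede the purchase. Model 3 uses no baseline outcome.
- *Section 3.6 prescribes follow-up-only outcomes and the models break it.* Its opening sentence reads that way, but the later text of the section builds the outcomes from baseline data, and the primary objective, the introduction to section 3.8 and the model descriptions also include baseline. This is an inconsistency of wording to be reconciled; it does not show that baseline was meant to be left out.

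It can also be said that dropping baseline altogether discards valid records from experienced users and is not a full cure. Someone who begins in month 2 is scored non-adherent at month 3 for encounters before starting. That objection is right, and it shapes the fix.

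**Conclusion.** The point holds for ED users: mainly Model 1, and to a lesser degree the ED Model 2. Applied as written, the rule gives wrong outcome values for people who began PrEP inside the recall window and had sex earlier in it, and no planned covariate corrects them. Baseline ED prevalence is understated, and associations with factors that differ between new and experienced users can be distorted.

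A reader might infer that the odds ratios are biased by a known amount. The documents do not support that. The new-starter share and its link to each factor are not given, and a null factor unrelated to being new stays at 1.00. The lag distribution, encounter rate and shares used above are assumptions, so the prevalences and odds ratios are illustrative. The scoring defect itself follows from the text and needs none of them.

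**What to change.** 1. Add one question on the date of first PrEP use.
2. At every visit, count an ED adherence record only if first use precedes the start of its recall window. Otherwise set it to missing, or limit the adherence questions to encounters since first use. Applying this at follow-up too covers people who begin after baseline.
3. Enter new or experienced status at baseline as a covariate.
4. Report Models 1 and 2 on follow-up visits only as a sensitivity analysis (Model 1: 3 and 6 months; Model 2: 1, 3 and 6 months).
5. Reconcile the opening sentence of the Primary Outcome text in section 3.6 with its later text, the primary objective and section 3.8, so that the role of baseline is stated once.

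The cost is one extra question, revised wording, and the loss of some records from recent starters, mostly at baseline. If the start date is not collected, the affected records cannot be identified afterwards.
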